## Methods

### Objective

The aim of this study was to develop a protocol to (1) evaluate the anti-fatigue effects of GJD in acute fatigue; (2) verify the mechanisms underlying the observed effects by assessing changes in stress hormones, oxidative stress-related biomarkers, homocysteine, and immunological factors; and (3) clinically assess the effectiveness and safety of GJD in treating acute fatigue using the Korean version of the Fatigue Severity Scale (FSS-K), Brief Fatigue Inventory (BFI-K), and Leeds Sleep Evaluation Questionnaire (KMLSEQ) scores as well as carrying out daily fatigue and sleep evaluations and assessments of heart rate variability (HRV) and adverse events.

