#### Secondary outcome

Salivary cortisol levels, the secondary outcome of this study, will be measured once at admission on day 1 at 21:00, and three times daily on days 2–4; for example, cortisol will be measured within 30 min of waking, at 12:00, and at 21:00. Subjects will not eat within approximately 1 h or brush their teeth within 10 min before saliva collection in order to avoid contamination.

Blood samples for analysis of epinephrine, norepinephrine, oxidative stress-related biomarkers (reactive oxygen species (ROS), nitric oxide (NO), malondialdehyde (MDA), protein carbonyl, glutathione (GSH), GSH reductase (GSH-Rx), superoxide dismutase (SOD), catalase, and total antioxidant capacity (TAC)), homocysteine, and immunological factors (tumour necrosis factor (TNF)-α, interferon (IFN)-γ, interleukin (IL)-2, IL-10, IL-12, T cells, B cells, and natural killer (NK) cells) will be collected at the same time as the serum cortisol samples. Complete blood counts will be conducted to quantify the populations of T cells, B cells, and NK cells during phase II, day 2.

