In the afternoon of days 1–4, HRV testing will be performed to study variations in the autonomic nervous system responses relevant to fatigue, where HRV is measured as variations in the beat-to-beat intervals; R is a point corresponding to the peak of the QRS complex of the electrocardiogram (ECG) wave and RR is the interval between successive Rs. For HRV assessments, 5 min of ECG signalling will be measured and calculated using a Neo Dinamika system (MR Co. Ltd., Gyeonggi-do, Republic of Korea). The HRV measurements will be taken after participants rest for 10 min, and the subjects will be seated comfortably in a chair in a quiet and bright room at 20–25 °C for the assessment. The equipment will be connected to the medial side of both wrists and ankles as well as to the insides of both wrists and the right ankle. Rhythm parameters of the HRV include pulse rate, vegetative balance index, rhythm vegetative factor, regulation process adequacy index, and tension index. Vegetative regulation parameters of the HRV include regulation level and regulation reserves. Statistical analysis of the HRV includes the RRNN (mean of normal-to-normal (NN) intervals, which is all intervals between adjacent QRS complexes); the SDNN (standard deviation of NN intervals); CV (coefficient variation); the RMSSD (the root mean square of successive NN interval differences); the NN50 (the number of interval differences of successive NN intervals greater than 50 ms); and the pNN50 (the proportion of NN50 divided by total number of the mean of all normal NN intervals). Spectral analysis includes HF (high frequency, 0.15–0.4 Hz), LF (low frequency, 0.04–0.15 Hz), VLF (very low frequency, 0.0033 to 0.04 Hz), normalised HF, normalised LF, LF/HF ratio and TP (total power).

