### Sample size

No previous clinical trials for serum cortisol levels from which sample size could be calculated have been reported; however, we consider a sample size of 24 to be a practical number for detection of clinically important differences between treatment and control groups. This number of subjects (12 per group) is the recommended minimum number per group for pilot studies [23]. We judged that this pilot study recommendation is applicable to feasibility study described here. Based on the results of this study, pilot trials will be needed in order to calculate appropriate sample size.

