The primary outcome analysis (*Δ = D*_*GJD*_*– D*_*PL*_) will be performed in two stages. First, a linear mixed effect model will be applied to assess the effect of treatment, sequence, and period with the random effect for subjects. The carryover effect due to preceding the treatment stage will then be estimated by testing the effect of sequence in the model. The linear mixed model will be modified by confounding the sequence effect to the error term if the carryover effect is not significant. Otherwise, the model will be rebuilt based on data collected in the first phase of the study. An analysis of variance (ANOVA) table for the model will be provided and least square means and their standard errors (95 % confidence intervals) will be reported for each treatment. Second, if the structure of data is balanced and the carryover effect is invalid, simple paired two-sample *t* tests or Mann Whitney *U* tests will be performed to evaluate the effect of GJD. The results will be shown as means and standard deviations for each treatment group and mean differences between the two treatments (95 % confidence interval) will be reported.

The analysis of secondary outcomes will be focussed on changes of measures within each treatment group from the baseline to the end of study. Again, the linear mixed effect model will be applied. The level of significance will be set to 0.05 (two-tailed) and all analyses will be performed with PROC MIXED and PROC GLM in SAS software, version 9.4 (SAS Institute Inc., Cary, NC, USA).

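### The protocol promises to verify GJD's mechanism from 20 secondary blood markers, with one 0.05 level for everything, no key marker and no criterion, so isolated significant markers cannot support that claim

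*Protocol article*

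**What the plan says.** - **Objective (Methods).** The second aim is to "verify the mechanisms underlying the observed effects by assessing changes in stress hormones, oxidative stress-related biomarkers, homocysteine, and immunological factors". The Abstract and the Background also use the word verify for the mechanisms, each time in a sentence that describes the work as exploring outcomes.
- **Secondary outcome.** The inputs begin with "Blood samples for analysis of epinephrine, norepinephrine, oxidative stress-related biomarkers" and continue through homocysteine, cytokines and lymphocyte subsets. All are treated alike; none is marked as key.
- **Statistical analysis.** "The level of significance will be set to 0.05 (two-tailed) and all analyses will be performed with PROC MIXED and PROC GLM". This sentence does not separate the primary outcome from the secondary ones. The sentences before it direct the secondary analysis at change from baseline within each treatment group, using the linear mixed model.
- **Sample size.** There are 24 participants, on a rule of thumb: "This number of subjects (12 per group) is the recommended minimum number per group for pilot studies".
- **Discussion.** The trial is described as a feasibility study without power to establish effectiveness, and its results are meant to inform later trials.

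**The concern.** Verifying a mechanism is a confirmatory claim. Here it rests on 20 candidate markers, each open to a nominal 5% test, with no statement of how many must move, which ones, or in which direction. Someone who follows the text could find one marker below 0.05 and report the mechanism as verified.

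At stake is the second objective and what is carried forward. If a chance marker is presented as the verified pathway, the next trial may be built around it. The primary serum cortisol comparison is not affected, because it is a single named outcome.

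**Working it through.** **Plan's own figure.** There is none to reproduce. The sample size of 24 is 2 × 12 from a rule of thumb, and no power or error rate for the marker panel is stated.

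**Inputs.**
- Level: 0.05 two-sided per test (Statistical analysis).
- Participants: 24, crossover (Sample size).
- Markers (Secondary outcome): epinephrine and norepinephrine, 2; ROS, NO, MDA, protein carbonyl, GSH, GSH-Rx, SOD, catalase and TAC, 9; homocysteine, 1; TNF-α, IFN-γ, IL-2, IL-10 and IL-12, 5; T, B and NK cells, 3. Total 2 + 9 + 1 + 5 + 3 = 20. Serum cortisol is left out because it is the primary outcome.
- Correlation between markers: not given in the document. Assumed, and varied.

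**Step 1: independent tests, no GJD effect, valid GJD versus placebo test for each marker.**
- Expected false positives: 20 × 0.05 = 1.0.
- P(at least 1) = 1 − 0.95^20 = 1 − 0.358 = 0.642.
- P(at least 2) = 1 − 0.358 − 20 × 0.05 × 0.95^19 = 1 − 0.358 − 0.377 = 0.264.
- P(at least 3) = 0.075.

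The exact count matters little. With 17 serum analytes (no cell subsets), P(at least 1) is 1 − 0.95^17 = 0.58; with salivary cortisol added as a 21st marker it is 1 − 0.95^21 = 0.66.

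**Step 2: correlated tests.** Twenty paired t tests on 24 participants were simulated 10,000 times under no effect.

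| Assumed correlation | P(at least 1) | P(at least 2) |
|---|---|---|
| common 0.3 | 0.55 | 0.24 |
| common 0.5 | 0.44 | 0.21 |
| common 0.7 | 0.29 | 0.16 |
| common 0.9 | 0.16 | 0.11 |
| 0.5 within marker families, 0.1 between | 0.55 | – |
| 0.7 within marker families, 0.3 between | 0.44 | – |

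The chance of at least one falls below one half somewhere between a common correlation of 0.3 and 0.5. Even at 0.9 it is about three times the nominal 5%.

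**Step 3: the contrast.** Steps 1 and 2 grant a valid between-treatment test. The stated focus on within-group change is weaker still. Suppose sleep restriction alone shifts a marker by 0.3 SD of change (an assumption). A within-GJD test on 24 participants is then significant with probability 0.29, and P(at least 1 of 20) = 1 − 0.71^20 ≈ 0.999 for independent markers, with no drug effect. Adjusting the significance level would not cure this, so the fix must also name the contrast.

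**Step 4: what error control would do.** Benjamini-Hochberg at 5% within five separate families would still leave 1 − 0.95^5 = 0.23 as the chance of some false positive under a complete null with independent families. Applied once to all 20 markers, that chance is 0.05 under independence. A single marker standing alone would then need p ≤ 0.05/20 = 0.0025. At that level the difference detectable with 80% power in 24 pairs rises from 0.60 to 0.88 SD of the paired differences.

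**The case against.** The strongest reply has three parts.

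1. **Silence is not a rule.** This is a condensed article and the statistical analysis plan is not shown. Multiplicity for secondary outcomes is commonly settled there. A reader might infer that the protocol commits to unadjusted testing; it does not say so. This stands, and the absence of a multiplicity procedure is not the point made here. The point is what is written: a verification objective beside one level for all analyses. An analysis plan that added adjustment would leave the objective's wording in place.

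2. **It is a feasibility study.** Nominal p-values for secondary outcomes in 24 people are ordinary practice, and the article itself speaks of exploring. This stands as a reason not to demand strict error control for every secondary outcome. It does not rescue the word verify: the Discussion's disclaimer concerns power for effectiveness and does not relabel the marker tests as exploratory.

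3. **The size can be overstated.** A reader might infer that the mechanism objective would probably be met by chance. The document does not support that. It never says one marker is enough; if two are needed the chance is 26% under independence, and with one marker it drops below 50% at moderate common correlation. A reader might also count every secondary measure, about 50, and quote a false-positive chance of about 93% (1 − 0.95^51). That does not describe the mechanism objective. Heart rate variability and the fatigue and sleep scales are placed under the third objective, and several of the variability parameters are tied to one another by definition (for example NN50 and pNN50), so independence cannot hold for them.

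**Conclusion.** The concern holds in a limited form. As written, the protocol allows a verified-mechanism claim from isolated significant markers, and such markers cannot support it. The chance of at least one false signal among the 20 is 64% under independence and about 55%, 44% or 29% at a common correlation of 0.3, 0.5 or 0.7; two or more occur in 26% under independence. These figures assume no GJD effect, valid 5% GJD versus placebo tests, and correlations that are mine and not the document's. They measure how easily one marker can turn up by chance; they are not the probability that the objective is met, because the protocol never defines that. The within-group focus of the secondary analysis makes the reading less safe, not more. The primary comparison is unaffected.

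**What to change.** 1. In the Abstract, the Background and the Objective section, replace verify with explore where the mechanisms are concerned.
2. In the Statistical analysis section, reserve the 0.05 decision level for the primary serum cortisol comparison.
3. In the same section, state that every secondary outcome will be reported as the GJD minus placebo difference with a 95% CI from the crossover mixed model, and that secondary p-values are hypothesis-generating.
4. Only if a mechanism claim is to be kept: apply Benjamini-Hochberg at 5% once, across the single family of 20 markers belonging to the second objective, homocysteine included, and not separately in five families. State beforehand what pattern of surviving markers would count as support.

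The cost is a few sentences and a few lines of code, with no new data or participants. The downside is that fewer individual markers can be called significant; under item 4 a marker standing alone would have to reach 0.0025.

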### Data and safety monitoring

Regular monitoring will be conducted to ensure quality control of the data according to the planned protocol and standard operating procedures. Monitors blinded to the allocation information will evaluate whether the recruitment procedures are correctly performed and whether the data are adequately recorded according to the protocol in the case report forms. If there are necessary changes to the study methods such as changes to the eligibility criteria, treatment regimens, or follow-up periods, the investigators will discuss these potential changes with independent researchers and statisticians. In the event that severe adverse events and crucial issues occur, the investigators will determine whether these issues are acceptable or if the trial should be amended or ended.

### Safety and adverse events

For the safety of study participants, complete blood counts, liver function tests, and urine analyses will be performed at the screening phase and the end of phases I and II, and vital signs will be checked once daily. Contact information will be provided to all participants for reporting of adverse events at any time. Practitioners will also check for any expected or unexpected adverse events every evening of the hospitalisation periods. Adverse events known to be related to GJD treatment include gastric discomfort, anorexia, nausea, diarrhoea, rash, urticaria due to drug-related allergic reaction, minimal-change disease, and acute focal tubulointerstitial nephritis [24]. Any adverse events reported by participants will be recorded for a causal relationship in the ‘Adverse event record table’. A causal relationship between the GJD or placebo treatment and adverse events will be evaluated using a six-grade scale (1 = definitely related, 2 = probably related, 3 = possibly related, 4 = probably not related, 5 = definitely not related, and 6 = unknown) and the seriousness of any such events will be scored using a three-point scale (1 = mild, 2 = moderate, and 3 = severe). Any adverse events will be reported in accordance with the regulations of the Institutional Review Board.

### Ethics

This study complies with the principles of the Declaration of Helsinki and Good Clinical Practice guidelines. The protocol has been reviewed and approved by the Institutional Review Board of the Daejeon Korean Medicine Hospital of Daejeon University (DJOMC-127-1) and is registered with the national clinical trial registry Clinical Research Information Service, which is a primary registry of the World Health Organisation International Clinical Trials Registry Platform (http://apps.who.int/trialsearch/Default.aspx; CRIS registration No. KCT0001681). Any protocol modifications will be approved by the Institutional Review Board of the Daejeon Korean Medicine Hospital of Daejeon University.

Written informed consent will be obtained from all study participants prior to enrolment into the study and participants will be given the option to decline to participate or withdraw at any time without disadvantage.

## Discussion

Deciding on the appropriate primary outcome of a trial is one of the challenges of trial design. The primary outcome in this study protocol is serum cortisol level measured at 30 min after waking. Cortisol is closely related to fatigue and blunted cortisol levels are primarily observed in patients with fatigue [25–27]. Although fatigue is a subjective symptom, cortisol levels were selected as the primary variable over the questionnaire-derived results.

Cortisol should be measured at the same time every day due to circadian rhythm. Cortisol levels may, moreover, be affected by dietary supplements [28], caffeine [29], and intensive exercise [30], as well as foods with a high sugar, fat, or protein content [12, 13]. The crossover method and participant hospitalisation were implemented in this study to minimise confounding factors and other possible bias [31].

To determine perceived symptoms and to compare these with objective outcomes, the results of self-reported questionnaires including the FSS-K, BFI-K, KMLSEQ, and daily fatigue and sleep evaluation questionnaires will be evaluated.

Epinephrine, norepinephrine, and HRV are related to the autonomic nervous system and as such are stimulated as a response to stress in the human body. Most individuals experiencing fatigue have hyperactive sympathetic nerves and hypoactive parasympathetic nerves [32, 33], and variations in autonomic nerve activity in the fatigue state can be observed as changes in serum concentrations of epinephrine and norepinephrine as well as in HRV [34].

In comparisons of normal individuals to those experiencing fatigue, it has been reported that circulating oxidative stress increases with fatigue, but that antioxidant levels decrease [35–37]. Immunity disturbances have been researched for potential involvement in chronic fatigue syndrome and analysis of immunological factors are, therefore, also included in this study [38, 39].

This is a feasibility study and is, thus, not powered to determine treatment effectiveness. As appropriate sample size could not be determined due to a lack of similar previous studies, the minimal sample size considered clinically significant was defined. The results of this study may, therefore, affect generalisability in other environments. Moreover, because fatigue will be artificially induced in healthy people in this study, the findings would not represent chronic fatigue, which is more clinically relevant. Further study with exact sample sizes in patients complaining of chronic fatigue would be necessary and could be designed based on the results from this study. This study protocol represents a unique opportunity to enhance our understanding of fatigue and the effects GJD on fatigue in terms of endocrine and immunological mechanisms and may, therefore, serve to improve future treatment strategies for chronic fatigue.

### Trial status

Recruitment for this trial opened in September 2015 and will close in December 2015. At the time of manuscript submission, the trial was in the recruitment phase.

## Abbreviations

ALT: Alanine aminotransferase
ANOVA: Analysis of variance
AST: Aspartate aminotransferase
BFI-K: Brief Fatigue Inventory-Korean version
CAM: Complementary and alternative medicine
CV: Coefficient variation
ECG: Electrocardiogram
ELISA: Enzyme-linked immunosorbent assay
FAS: Full analysis set
FSS-K: the Fatigue Severity Scale-Korean version
GJD: *Gongjin*-*dan*
GSH: Glutathione
GSH-Rx: Glutathione reductase
HF: High frequency
HRV: Heart rate variability
IL: Interleukin
INF-γ: Interferon gamma
ITT: Intention-to-treat
KMLSEQ: Korean Version of the Modified Leeds Sleep Evaluation Questionnaire
LF: Low frequency
MDA: Malondialdehyde
MFDS: Ministry of Food and Drug Safety
NK cells: Natural killer cells
NN intervals: Normal-to-normal intervals
NN50: Number of interval differences of successive NN intervals greater than 50 ms
NO: Nitric oxide
pNN50: Proportion of NN50 divided by total number of the mean of all normal NN intervals
PP: Per-protocol
PSQI-K: Pittsburgh Sleep Quality Index-Korean version
RMSSD: Root mean square of successive NN interval differences
ROS: Reactive oxygen species
RRNN: Mean of normal-to-normal intervals, which is all intervals between adjacent QRS complexes
SDNN: Standard deviation of NN intervals
SOD: Superoxide dismutase
TAC: Total antioxidant capacity
TNF-α: Tumour necrosis factor alpha
TP: Total power
VAS: Visual Analogue Scale
VLF: Very low frequency
